# 12. PARTICIPANT EXPERIENCE QUALITATIVE ASSESSMENT

## 12.1 Participant experience

A sample of participants will be invited to join focus groups to be conducted approximately 3, 6 and 12 months after randomisation. These groups are designed to understand the issues participants may have had accessing tinnitus care before the trial, the way they interacted with the trial interventions, any areas of the interventions that could be improved, and finally to discuss how these interventions may be introduced to the NHS. The focus group data will be used to aid interpretation of the quantitative study data and the health economic evaluation, and at the end of the trial will be disseminated alongside the main trial results.

## 12.2 Sampling

The DEFINE Trial Manager will generate a list of participants who have consented to further contact for the focus group. Targeted sampling will be conducted 4 months after the start of recruitment, and then further rounds will be undertaken 3 and 9 months later. Participants will not be selected for more than one focus group timepoint. Where possible the selected sample will be weighted to Office of National Statistics criteria for a nationally representative group based on several variables (age, sex, ethnicity, geographical region), and also balanced across the randomised intervention given, and severity of tinnitus. Investigators will contact those in the sample list via email and/or phone until the required number of participants at each time point is reached.

## 12.3 Focus group consent

Consent for focus group participation and data analysis is included as an optional item on the main DEFINE study consent form.

The transcript data from consenting individuals may additionally be used for publication/media release in journals, newspapers, radio, interviews, TV, social media, websites, newsletters, marketing in print and online. Participants will be provided with a list of the above media types, and asked if willing to consent to use in all or specific dissemination formats.

## 12.4 Focus group design

Focus groups will be semi-structured based on a topic guide. Three focus groups, with 4 participants in each group and lasting up to 60 mins each will be conducted online using Microsoft Teams software. One group will be conducted in the morning, a further in the afternoon, and the final in the evening in an attempt to accommodate a range of individuals. As with sampling, groups will be mixed so that they vary in participant age, sex, ethnicity, geographical location and tinnitus severity. Video recordings will be made using MS teams to record the focus group discussion in its entirety and the transcript will be downloaded following the session.

All participants will be reminded before participation that they will be in an online group situation and accordingly, will be identifiable to the other participants.

A trained facilitator who is part of the DEFINE trial team will coordinate and guide the focus groups.

## 12.5 Focus group topics

A semi-structured topic guide will be used by the facilitator to initially engage participants in key topics and prompt focussed discussions. The topic guide will be designed based on clinical experience of the investigators, and those who deliver CBT and developed the Oto programme. Our PPIE group will also be consulted on topic guide development. The guide will explore:

- barriers to seeking and obtaining advice and treatment for tinnitus
- participant ideas, concerns and expectations about the trial interventions
- the way participants interacted with the trial interventions
- suggested improvements to the delivery or content of the trial interventions
- how these interventions may best be deployed within the NHS

# 13 DATA MANAGEMENT

## 13.1 Source Data

Source data are where data are first recorded, and from which participants’ survey data are obtained. These include, but are not limited to, medical records, pharmacy records, participant surveys, and correspondence.

EDC entries will be considered source data if the EDC is the site of the original recording. All documents will be stored securely and safely in confidential conditions.

## 13.2 Access to Data

Data will be entered into a validated EDC platform. Direct access to the EDC platform will be granted to authorised representatives from the Sponsor and Lindus Health to allow trial-related monitoring and/or audits to ensure compliance with regulations. Access to this system will be strictly on a need to know basis and the system will be on a secure server. To ensure data transparency, the trial will be registered on a publicly available database for clinical studies.

## 13.3 Data Handling and Record Keeping

The data management will be run in accordance with Lindus Health SOPs, which are fully compliant with Good Clinical Practice (GCP), GDPR and the Data Protection Act 2018. Research data will be de-identified upon collection. Identifiable information will be stored separately from the research data.

A unique trial specific number and/or code in the database will identify the participants.

An online secure data entry system designed to collect sensitive data, such as participant and Study Partner contact details, will be used. All identifiable participant data is encrypted using the Advanced Encryption Standard. The participant portal will also manage online ePRO.

Informed consent (e-consent) will be completed using worksheet templates, which will be retained in a secure area with restricted access. The remaining data, including reconfirmation of consent and records of eligibility confirmation will be collected directly onto the EDC platform, therefore no further source will be available.

Identifiable participant data will be kept for 12 months beyond the end of the study. Non-identifiable participant data will be maintained for a minimum of ten years unless otherwise required to comply with legislation or regulation and reviewed on an annual basis.

# 14. QUALITY ASSURANCE PROCEDURES

The study may be monitored, or audited in accordance with the current approved protocol, GCP, relevant regulations and standard operating procedures.

## 14.1 Risk Assessment

The risk assessment and categorization tool will be used to identify and evaluate potential risks to participant safety, data quality, and study integrity, and to determine the appropriate risk mitigation strategies. This tool will include an assessment of various aspects of the study, such as participant recruitment, data collection, and intervention administration. The tool will be reviewed and updated throughout the study to ensure ongoing risk management.

## 14.2 Study Monitoring

Monitors may verify that the clinical study is conducted, and data are generated, documented and reported in compliance with the protocol, GCP and the applicable regulatory requirements. Specifics will be detailed in the Trial Monitoring Plan.

## 14.3 Study Committees

A Trial Steering Committee (TSC) and Trial Management Group (TMG) will be appointed. The responsibilities of each group are as follows:

TSC- to review the safety data and to review and monitor the accruing data to ensure the rights, safety and wellbeing of the trial participants. They will make recommendations about how the study is operating and any ethical or safety issues. This Committee will also take on the role of a Trial Steering Committee, and so act as a single oversight committee meeting at least bi-annually.

Trial Management Group (TMG)- is responsible for the day-to-day running of the trial, including monitoring all aspects of the trial and ensuring that the protocol is being adhered to. It will include the Lindus Health Clinical Operations Team, Medical Lead and Product Manager working closely with the CI and Sponsor and will meet weekly in the first instance. After the initial weekly meetings, the TMG will meet on a regular basis, such as monthly or bi-monthly, to discuss study progress and address any issues that may arise.

# 15. PROTOCOL DEVIATIONS

A study related deviation is a departure from the ethically approved study protocol or other study document or process (e.g. consent process or administration of study intervention) or from Good Clinical Practice (GCP) or any applicable regulatory requirements. Any deviations from the protocol will be documented, assessed as to whether it is a potential Serious Breach (according to the definition in Section 15) and filed in the electronic Trial Master File (eTMF), according to Lindus Health SOPs. All protocol deviations will be recorded in a Protocol Deviation Tracker and discussed with the CI and Sponsor on a regular basis during the course of the study.

# 16. SERIOUS BREACHES

A “serious breach” is a breach of the protocol or of the conditions or principles of Good Clinical

Practice which is likely to affect to a significant degree

(a) the safety or physical or mental integrity of the trial participants; or

(b) the scientific value of the research.

In the event that a serious breach is suspected the Sponsor must be contacted within one working day. In collaboration with the CI, the serious breach will be reviewed by the Sponsor and, if appropriate, the Sponsor will report it to the approving REC committee within seven calendar days.

# 17. ETHICAL AND REGULATORY CONSIDERATIONS

## 17.1 Declaration of Helsinki

The Investigator will ensure that this study is conducted in accordance with the principles of the Declaration of Helsinki (2013).

## 17.2 Guidelines for Good Clinical Practice

The Investigator will ensure that this trial is conducted in accordance with relevant regulations and with Good Clinical Practice.

## 17.3 Approvals

The protocol, informed consent form, participant information sheet and any proposed advertising material will be submitted to an appropriate Research Ethics Committee (REC) and HRA for written approval. The Investigator will submit and, where necessary, obtain approval from the above parties for all substantial amendments to the original approved documents. Substantial amendments are those that have a significant impact on the safety or welfare of the participants, the scientific value of the study, or the conduct or management of the study.

## 17.4 Reporting

An Annual Progress Report will be submitted once a year to the REC, HRA (where required) and Sponsor. In addition, an End of Trial notification and final report will be submitted to the REC and Sponsor.

## 17.5 Participant Confidentiality

The trial staff will ensure that the participants’ anonymity is maintained. The participants will be identified only by a participant ID number on all trial documents and in the electronic clinical database. All data will be stored securely on an electronic study database and will comply with the General Data Protection Regulation (GDPR) and Data Protection Act 2018, which require data to be de-identified as soon as it is practical to do so. The study database will be managed according to Standard Operating Procedures maintained by Lindus Health. Access rights to data and applications software will be clearly defined and staff authorised to access personal data will be formally notified in writing of the permissible scope of their access. Data access will be limited to specific members of the research team (trained in data protection policy) including the chief investigator (as study guarantor), and engineers. For each database application, system users will be given a valid user system account name (username ID), and a password known only to that user to prevent unauthorised use of systems. All data will be entered into the database through a reliably encrypted gateway.

## 17.6 Expenses and Benefits

Participants in the smartphone app delivered arm will receive free access to the intervention for the 12 months of the study. Those in the control group will receive a free subscription to the Oto tinnitus programme at the end of the 12 month trial period.

## 17.7 Patient and Public Involvement and Engagement (PPIE)

The Lindus Health Patient Advisory Board has provided substantial input to the protocol and the overall study design. A study PPIE group has been formed and provided input into patient facing materials including the study design, patient information sheet, information video and informed consent form. The EDC platform has undergone user testing to ensure that it is user friendly and the language is understood.

# 18. FINANCE AND INSURANCE

## 18.1 Funding

This study will be funded by Innovate UK (UKRI) (70%) and Oto Health (30%) and conducted by Lindus Health.

## 18.2 Insurance

The Sponsor has a specialist insurance policy in place for this study which would operate in the event of any participant suffering harm as a result of their involvement in the research.

## 18.3 Contractual Arrangements

Appropriate contractual arrangements with third parties will include agreements covering the provision of goods and services, data sharing and management, and intellectual property rights, among other matters. These contracts will be established to ensure that all parties are aware of their roles and responsibilities and to protect the interests of the study and its stakeholders.

# 19. PUBLICATION POLICY

The Chief Investigator will lead the collaborative drafting of the manuscripts, abstracts, press releases and any other publications arising from the study. Authors will acknowledge that the study was delivered via a clinical trial agreement between Oto Health and Lindus Health. Authorship will be determined in accordance with the International Committee Medical Journal Editors guidelines and other contributors will be acknowledged.

The study results will be published in an open-access journal or repository, ensuring that the research findings are accessible to a wide audience, including healthcare professionals, researchers, and the public.

No publication or disclosure of study results will be permitted except under the terms and conditions of a separate written agreement between Oto Health and the CI.

# 20. ARCHIVING

Study materials will be archived according to Lindus Health SOPs for a minimum of ten years, personal data will be retained for a minimum of 12 months, compliant with applicable legislation and trial regulations.

# 22. APPENDIX 1 – TRIAL FLOW-CHART

| **Recruitment**  Primary care, social media, patient communities |
| --- |

↓

| **Prescreening and Registration**  Potential participants directed to LH website. Registered in the LH system. PIS, ICF, video emailed, screening call booked |
| --- |

↓

| **Enrolment**  Potential participants checked against I/E criteria, consent confirmed, randomised to study arm. |
| --- |

↓

| **Sponsor, Participant, GP notified**  Details of randomised participants shared and enrolment confirmed |
| --- |

↓

| **Intervention Arm**  Onboarded to the Oto Tinnitus Programme for 6W | **←** | **Treatment Phase Begins**  Participants enrolled on schedule of assessments and baseline collected | **→** | **Control Arm**  Therapist delivered CBT by a trained specialist |
| --- | --- | --- | --- | --- |

↓

| **Month 1 Follow Up**  Remote contact for outcome measurements |
| --- |

↓

| **Month 3 Follow Up**  Remote contact for outcome measurements |
| --- |

↓

| **Month 6 Follow Up**  Remote contact for outcome measurements |
| --- |

↓

| **Month 12 Follow Up**  Remote contact for outcome measurements |
| --- |

↓

| **End of Trial** |
| --- |

# 23. APPENDIX 2 - SCHEDULE OF EVENTS TABLE

| **Procedure** | **Pre-screener**  Week -*N* | **Screening**  Week 1, Day 0 | **Randomisation**  Day 0 | **Baseline**  Week 1, Day 1 (+ 7 days) | **Oto App starts for 6wks / consultation for CBT booked**    Day 1 | **Month 1 Follow Up**  Week 4, Day 1 (+/- 7 days) | **Month 3 Follow Up**  Week 12, Day 1 (+/- 14 days) | **Month 6 Follow Up**  Week 24, Day 1 (+/- 14 days) | **Month 12 Follow Up**  Week 52, Day 1 (+/- 28 days) |
| --- | --- | --- | --- | --- | --- | --- | --- | --- | --- |
| Informed Consent | ✓ | ✓ |  |  |  |  |  |  |  |
| Eligibility assessment | ✓ | ✓ |  |  |  |  |  |  |  |
| Medical history | ✓ | ✓ |  |  |  |  |  |  |  |
| Demographics |  | ✓ |  |  |  |  |  |  |  |
| Tinnitus Background Survey |  |  |  | ✓ |  |  |  |  |  |
| Tinnitus Functional Index (TFI) |  |  |  | ✓ |  | ✓ | ✓ | ✓ | ✓ |
| EQ-5D-5L |  |  |  | ✓ |  |  | ✓ | ✓ | ✓ |
| HUI3 |  |  |  | ✓ |  |  | ✓ | ✓ | ✓ |
| Resource Use Questionnaire |  |  |  |  |  | ✓ | ✓ | ✓ | ✓ |
| System Usability Scale |  |  |  |  |  |  | ✓ |  |  |
| AE review |  |  |  | ✓ |  | ✓ | ✓ |  |  |
| Study Experience Questionnaire |  |  |  |  |  |  | ✓ | ✓ | ✓ |
| Adherence Data collected (eCRF) |  |  |  |  |  | ✓ | ✓ | ✓ | ✓ |

#

#

#

#

#

#

#

# 24. APPENDIX 3 – CONTROL ARM INTERVENTION SPECIFICATION

Control arm intervention – specification

The standard care intervention was developed based on relevant guidance (BSA Practice Guidance Tinnitus in adults 2021 and NICE guidelines (NG-155)) and via consultation with clinicians providing NHS tinnitus therapy.

New assessment (approximately 60 minutes) to include:

1. Information gathering and education

- Detailed audiological history to include onset, progression, nature and impact of tinnitus at home/work/social, on sleep, mental health and quality of life.
- Explanation of tinnitus, tailored to the patients’ needs and understanding, usually based on a neurophysiological model (Jastreboff PJ, 1990) or cognitive behavioural model (McKenna et al 2014)
- Explanation of how hearing loss may influence tinnitus awareness
- Discussion of options for treatment/ rehabilitation

Questionnaires should be administered as appropriate to assess tinnitus handicap, anxiety and depression in order to establish the functional impact of tinnitus and guide appropriate management, and if appropriate onward referral to other specialties. Example questionnaires for this purpose include: Tinnitus Handicap Inventory; Tinnitus Functional Index; Hospital Anxiety and Depression Scale; Insomnia Severity Index

2. Individual Management Plan

These should be formulated individually, agreed with the participant and may include:

- Relaxation Therapy: Exercises, apps, refer to physio where indicated/available
- CBT: where available. Clinicians may undertake CBT if they have appropriate training and experience to do so. Others may suggest CBT exercises as part of therapy where appropriate, or signpost to other local services, where these exist.
- Signposting for equipment to facilitate sound enrichment and relaxation
  - - Sound generators with/ without pillow speakers
    - Ear level or in the ear sound generators
    - Relaxation CD
- Recommendation for hearing aid fitting where hearing loss is present and discussion of combination hearing aid/ tinnitus maskers where relevant
- Information leaflets which include websites with more information about tinnitus and products available
- Tinnitus UK
- Royal National Institute for the Deaf
- Treatment for anxiety/depression: signpost to local wellbeing service or to GP for antidepressant medication

Follow-up appointments if indicated (30 min routine/ 45 min complex) to include:

- Revision of history of changes
- Discussion/ documentation of progress and outcome of treatment plan
- Onward referral if appropriate
- Further follow-ups can be arranged as required and according to departmental policy.

At any stage in the intervention the therapist may consider onward referral if appropriate and after discussion with the participant

This could include the following:

- Audiology: hearing aid assessment and fitting, ear level sound generator fitting/ combi device fitting or further diagnostic tests
- GP: to request counselling or a formal psychological or psychiatric referral; medication review

o Where a patient has significant anxiety or depression and is judged to be at significant risk of self-harm, the GP should be contacted immediately by phone. The patient should be made aware of this and encouraged to see their GP urgently.

o If a patient has significant anxiety and depression but is not suicidal, then discuss a local referral with their GP, or self-refer for psychology support via Improving Access to Psychological Therapies.

- ENT: further tinnitus investigations, vestibular assessment
- Physiotherapy: relaxation exercises.

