# 2 STUDY SYNOPSIS

| Title | Digital thErapy For Improved tiNnitus carE |
| --- | --- |
| Short title | DEFINE |
| Chief Investigator | [name] |
| Background | Tinnitus is a common condition, affecting approximately 15% of UK adults. It is usually perceived as a buzzing or ringing in the ears, without a stimulus in the outside world. There is currently no cure, but cognitive behavioural therapy (CBT) has been shown to be effective in reducing self reported distress and illness severity. Unfortunately, access to CBT is limited, with significant healthcare costs associated with provision and additional costs to people with tinnitus including time away from work, travel and lost productivity. |
| Primary objective | To assess whether Oto’s digital tinnitus programme is no worse at reducing self-reported tinnitus severity as therapist-delivered CBT |
| Secondary objectives | - Assess whether Oto’s digital tinnitus programme is superior to therapist-delivered CBT in reducing self-reported tinnitus severity - Assess the self-reported impact of Oto’s digital tinnitus programme on aspects of participants tinnitus experience - Assess the impact on overall health-related quality of life of Oto’s digital programme and human delivered CBT - Assess the usability of the Oto digital programme - Explore participants views of the impact and usability of Oto’s digital programme - Understand the health economic consequences of using a digital therapeutic for tinnitus - Assess the number of adverse events between the groups - Assess intervention Adherence |
| Study design | An open-label, non-inferiority, prospective, parallel design, randomised-controlled study assessing the Oto smartphone tinnitus management programme versus therapist delivered CBT in achieving improvement in self-reported tinnitus severity in adults. |
| Phase | III |
| Setting | Fully decentralised study with participants recruited remotely. Interventions and assessments delivered remotely via the Oto health smartphone app, video calls and the Lindus Health platform. |
| Recruitment Strategy | Patients will be recruited centrally by the Lindus Health research team, with Lindus Health acting as a research site. Patients will be identified via primary care, advertising on social media and to patient communities, in addition to healthcare professionals directing potential participants to the trial website. Patients can receive £40 for taking part in the trial. |

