| Primary Outcome | Total TFI score (Score of 0-250 with high score indicating worse outcome) 6 months from starting therapy |
| Secondary Outcomes | 1) Total TFI and TFI subscale scores at 1, 3 and 12 months  2) Participant health-related quality of life measured using the EuroQol EQ-5D-5L and the Health Utilities Index Mark 3 (HUI3) responses and summary scores at 3, 6 and 12 months follow-up from starting therapy  3) Adverse events from randomisation to 3 months  4) System Usability Scale scores at 3 months  5) Qualitative feedback from focus groups and semi structured interviews at 3, 6 and 12 months  6) Cost-utility analysis synthesising costs and QALYs over trial period  7) Assess intervention adherence at 3 and 6 months |
| Number of participants | 196 participants, randomised in a 1:1 ratio |
| Eligibility criteria | Inclusion Criteria   1. Aged 18 years or over 2. Experienced tinnitus symptoms for at least 3 months and self-assessed as having a significant impact on quality of life. 3. Have access to a smartphone 4. Able and willing to give consent for the study prior to participation 5. Able to speak and read English to a sufficient level.   Exclusion Criteria   1. Tinnitus with potential “red flag” symptoms i.e. unilateral or pulsatile tinnitus (assessed via a red flag checklist during the screening call) 2. Significant mental health problems e.g. history of suicidal ideation or requirement for psychiatric/psychological support beyond Primary Care level 3. Have required hospitalisation for depression or taking antipsychotic drug 4. Currently taking part in another clinical trial for hearing/tinnitus 5. Awaiting surgical intervention for hearing/tinnitus 6. Previously undergone tinnitus therapy of any type e.g. CBT or TRT 7. Pregnant and breastfeeding women   Additional Note: Patients with hearing aids are eligible to participate in the study |
| Intervention | The Oto digital programme for tinnitus. This involves direct access to a digital multi-modal therapy package incorporating CBT, physical therapy, mindfulness and relaxation therapy. |
| Comparator | Current standard of care (1-1 therapist-delivered CBT). |
| Duration of study | 18 months |
| Randomisation / Blinding | Randomised 1:1 by computer algorithm and stratified by age, sex and level of hearing loss. Unblinded. |
| Statistical analysis | Non-inferiority |
| Intervention Adherence | Number of participants in each group completing therapy programme by 3 months |

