# 3 BACKGROUND and RATIONALE

3.1 Background

Tinnitus is the perception of sound in the absence of an external stimulus. Tinnitus is very common with approximately 15.3% of the UK population experiencing prolonged tinnitus with 5.4% considering this bothersome^1^. Prevalence varies with age, with approximately 10% of younger adults, 14% of middle aged adults and 24% of older adults experiencing tinnitus^2^.

Treatment options for people with tinnitus are currently suboptimal. The approach with the strongest evidence base is Cognitive Behavioural Therapy (CBT), with guided self-directed CBT showing the largest effect size and having the highest likelihood of being ranked first in improving tinnitus health-related quality of life (75%), depression (83%), and anxiety (87%)^3^. Current NHS provision as delivered by Ear, Nose and Throat Surgeons, Audiologist and Hearing Therapists, focuses on ensuring there are no concerning features, such may indicate cerebellopontine angle pathology or systemic health problems. Once these are ruled out, patients may be offered referral for tinnitus therapy. Provision of this therapy, both in terms of access and method of delivery, is inconsistent. Current NICE guidance advocates a combination of reassurance, mitigation of any underlying cause if possible, optional hearing aiding if concomitant hearing loss is present, self-care advice and consideration of referral for psychological therapy^4^.

Current NHS tinnitus therapy provision is typically based on the principles outlined in Tinnitus Retraining Therapy (TRT), though some elements of Cognitive Behavioural Therapy (CBT) and relaxation may also be incorporated. Provision outside the NHS is more varied, usually featuring longer term support and contact and a wider range of therapeutic techniques. This provision is typically on a one-to-one basis and lasts between one and ten sessions. However, many people with tinnitus do not access such support and an opportunity exists to expand provision to this underserved group as well as supplementing and optimising current provision for those able to access therapeutic support.

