# 4 OBJECTIVES AND OUTCOME MEASURES

4.1 Randomised Controlled Trial

Primary Objective

| **Objective** | **Outcome Measure** | **Timepoint(s) of evaluation** |
| --- | --- | --- |
| Assess whether Oto’s digital tinnitus programme is as effective at reducing self-reported tinnitus severity as therapist- delivered CBT | Total TFI score | Primary outcome is total TFI score at 6 months  TFI evaluated at:  Baseline, 1, 3, 6 and 12 months |

Secondary Objectives

| Objective | Outcome Measure | Timepoint(s) of evaluation |
| --- | --- | --- |
| Assess whether Oto’s digital tinnitus programme is superior to therapist-delivered CBT in reducing self-reported tinnitus severity | Total TFI score | Total TFI score at 6 months |
| Assess the self-reported impact of Oto’s digital tinnitus programme on aspects of participants tinnitus experience | 8 Tinnitus Functional Index subscales (Intrusive, Sense of Control, Cognitive, Sleep, Auditory, Relaxation, Quality of Life and Emotional). | Baseline, 1, 3, 6 and 12 months |
| Assess the impact on overall health-related quality of life of Oto’s digital programme and therapist delivered tinnitus therapy | EuroQol EQ-5D-5L and Health Utilities Index Mark 3 (HUI3) | Baseline, 3, 6 and 12 months |
| Assess the usability of the Oto digital programme | System Usability Scale | 3 months |
| Explore participants views of the impact and usability of the two interventions | Thematic analysis of focus groups and semi structured interviews | 3, 6 and 12 months |
| Understand the health economics of the two for tinnitus | Cost-utility analysis | Over trial period covering from baseline to 12 months |
| Assess the number of adverse events between the groups | eCRF | Randomisation to 3 months |
| Assess intervention Adherence | Number of participants completing the intervention | Number of participants starting the intervention at baseline compared to those completing the intervention at 3 and 6 months |

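### The control is named as therapist-delivered CBT, but its specification in Appendix 3 makes CBT optional; success supports a claim against CBT only if CBT is required or shown to have been delivered.

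*Protocol*

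**What the plan says.** The synopsis (section 2) sets the primary objective as showing the app to be "no worse at reducing self-reported tinnitus severity as therapist-delivered CBT" and gives the comparator as "Current standard of care (1-1 therapist-delivered CBT"). Section 3.2 equates current standard care with CBT delivered by a person, section 10.2 states the aim as non-inferiority to CBT, and the flow-chart in Appendix 1 labels the control arm as CBT from a trained specialist.

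The sections on delivery use different terms. Section 7.6 describes one-to-one tinnitus therapy from an audiologist or hearing therapist, given remotely, with at least one and at most six sessions, and refers to Appendix 3 for the specification. Section 8.2 adds psychologists to the possible providers. It says the therapy will include several elements of standard care and lists five, one of which is CBT.

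Appendix 3 requires a first appointment covering history, explanation and discussion of options. On the individual management plans it says: "These should be formulated individually, agreed with the participant and may include". The CBT entry in that list is "CBT: where available. Clinicians may undertake CBT if they have appropriate training and experience to do so", and for the remaining therapists "Others may suggest CBT exercises as part of therapy where appropriate, or signpost to other local services, where these exist".

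**The concern.** A non-inferiority conclusion is a statement about a particular comparator. The background section rests the case for treating tinnitus on the evidence for CBT, and the headline claim would be that the app is no worse than CBT from a therapist. If the control can be delivered as specified without CBT, the data do not by themselves support that claim. What is at stake is the wording of the conclusion and how a reader or commissioner would use it, not the mechanics of the test.

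**Working it through.** No arithmetic applies, so the check compares the texts.

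1. **Which text governs the control?** Section 7.6 names Appendix 3 as the specification of the therapy to be provided. Section 8.2 is a summary description. It sets no CBT content, dose or therapist qualification.

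2. **Does Appendix 3 require CBT?** No. Three conditions stand between a participant and CBT: the plan need not contain it, it must be available, and the clinician must have the training and experience. A clinician without that training may suggest exercises or point the participant to another service. Section 7.6 asks that panel members have experience of NHS tinnitus care; no section requires CBT training.

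3. **What is the least a control can receive as specified?** One session (sections 7.6 and 8.2), with follow-up appointments only if indicated (Appendix 3). One session of assessment and education with no CBT meets the specification.

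4. **Does the per-protocol analysis separate such participants?** Not reliably. Section 10.1 defines control compliance twice: in one place as one or more sessions for the group it calls the CBT group, in another as one or more sessions of CBT. Under the former definition the participant in step 3 is compliant. Under the latter, read literally, that participant is not, but step 5 shows that no named data item would identify them. The per-protocol analysis is in any case a sensitivity analysis; the primary analysis is by intention to treat.

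5. **Is CBT content recorded?** Section 8.2 has therapists report attendance and number of sessions. Appendix 2 schedules adherence data at months 1, 3, 6 and 12, and section 11.1 mentions delivery information in general terms. Appendix 3 foresees documenting progress of the treatment plan, but at follow-up appointments, which a one-session participant does not have. None of these commits to recording whether CBT was given.

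6. **Is CBT simply shorthand for usual NHS care?** Section 3.1 does not support that: "Current NHS tinnitus therapy provision is typically based on the principles outlined in Tinnitus Retraining Therapy (TRT"), with CBT elements that may also be used. The naming also varies within the protocol. For the same quality-of-life objective, the synopsis compares the "digital programme and human delivered CBT", while section 4.1 compares the "digital programme and therapist delivered tinnitus therapy".

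The stated objective and the specified control are therefore not the same comparator, and section 8.2 and Appendix 3 disagree on whether CBT is part of it.

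**The case against.** The strongest reply is section 8.2. Its natural reading is that the listed elements, CBT included, are delivered. The therapists are a selected panel, may include psychologists, and are described in the flow-chart as trained specialists. The pragmatic nature of the control is also disclosed: section 5.2 calls it usual care, section 7.6 says it will broadly follow NHS treatment, and Appendix 3 says it was built from NICE and professional guidance. Individualised standard care is a legitimate comparator, and detailed case-report content often sits outside a protocol.

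Much of this stands. The choice of control is not at fault, and section 8.2 prevents the reading that controls will go without CBT. A reader might infer from Appendix 3 that some or many controls will receive none; the documents do not show that any will. They leave it possible, and they conflict. Section 8.2 does not settle the conflict, because it speaks of several elements formed into a personal plan, its list includes hearing-aid signposting that not every participant needs, and it is not the named specification.

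A reader might also infer that the trial's type I error is inflated. It is not: the planned test keeps its 2.5% level against the control as specified. Any figure for wrongly concluding non-inferiority to CBT would need an assumed share of controls without CBT and an assumed effect of omitting it, and the documents give neither.

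**Conclusion.** The point holds as an inconsistency that limits the conclusion. As specified, success supports non-inferiority to remote one-to-one therapist-delivered tinnitus therapy of one to six sessions, with or without CBT. It supports a claim against CBT only if CBT is made a required part of the control or is shown to have been delivered. The size of the gap cannot be estimated from the protocol and could be nil if every therapist on the panel gives CBT. The verdict rests on taking Appendix 3 as governing, as section 7.6 says. If section 8.2 is taken as governing instead, the two texts still contradict each other and need reconciling. The trial remains valid; this should be corrected before results are reported.

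**What to change.** Reconcile the texts in one of two ways.

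- **(a) Keep CBT as the comparator.** Amend Appendix 3 to require CBT content, as section 8.2 implies, and keep control compliance in section 10.1 as one or more sessions of CBT, removing the looser wording.
- **(b) Keep the control as specified.** Reword the objective, comparator and permitted conclusion to remote one-to-one therapist-delivered tinnitus therapy in sections 2, 3.2, 4, 7.8, 10.1 and 10.2 and Appendices 1 and 2. Align section 8.2 with Appendix 3, and define control compliance once as one or more attended therapy sessions.

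Under either route, add one item to the therapist return described in section 8.2: CBT delivered, CBT exercises suggested, signposted elsewhere, or none. The control arm can then be described and the controls who had CBT identified.

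The cost is a protocol amendment, which may count as substantial under section 17.3, and one extra field on an existing return. Route (a) also requires therapists able to deliver CBT; route (b) gives a narrower claim. Neither route in itself alters the inputs to the sample-size calculation.
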